**Methods:**

One hundred seventy-six patients with clinical stage N0 (cN0) and pT1b ESCC will be recruited at three centers and randomly assigned to the esophagectomy group or the dCRT group. The clinical lymph node status will be measured by image examination, including computer tomography and positron emission tomography–computed tomography. The pathological tumor status will be diagnosed after endoscopic submucosal dissection (ESD). All patients will be followed up for 60 months after randomization. The primary endpoint is 5-year overall survival. The secondary endpoints are quality of life, related adverse events, 3-year overall survival, and relapse-free survival rates.

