### Trial design {8}

This study is a multicenter, randomized, open-label, phase III trial. All participants will be allocated to the two intervention groups at 1:1 ratio. The flow chart is illustrated in Fig. 1.

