### Sample size {14}

According to previous studies, the 5-year OS of patients with pT1b ESCC who underwent esophagectomy was 70 ~ 80% [23] whereas the rate was about 90% in patients who received ER plus chemoradiation [16]. We assumed that the 5-year OS rates were 75% in the esophagectomy group and 90% in the dCRT group. The proportion dropping out of the study is considered to be 5%. Therefore, a sample size of 88 patients in each group is required at a significance level of 5% and a power of 80%.

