### Statistical methods

#### Statistical methods for primary and secondary outcomes {20a}

Statistical analyses are performed using SPSS version 20.0 software (SPSS Inc., Chicago, IL, USA). The statistical analysis will be performed in accordance with both the intention-to-treat and the per-protocol principles. Survival will be estimated by Kaplan–Meier methods and analyzed using log-rank test. Continuous variables will be compared using a Student’s *t* test or Wilcoxon rank-sum test as appropriate and represented as the mean ± standard deviation or as median and range. Categorical variables will be compared using Fisher’s exact test or Wilcoxon rank-sum test as appropriate and represented as number of patients and percentage. For the analysis of QoL, parametric or non-parametric statistical methods will be used to assess the results of QLQ-C30 and QLQ-OES18 from pretreatment to 12 months, depending on the data distribution.

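### With 60 months of follow-up, 88 patients per group gives about 73–75% power for a two-sided 5% test, not 80%; the sidedness and method behind the figure are not stated

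*Protocol article*

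**What the plan says.** Sample size {14} gives the effect: "We assumed that the 5-year OS rates were 75% in the esophagectomy group and 90% in the dCRT group". On losses it says "The proportion dropping out of the study is considered to be 5" per cent. From these it concludes that "a sample size of 88 patients in each group is required at a significance level of 5% and a power of 80" per cent. Trial design {8} fixes the ratio: "All participants will be allocated to the two intervention groups at 1:1 ratio".

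The primary endpoint (Outcomes {12}) is 5-year OS in everyone randomised. The analysis (Statistical methods {20a}) is Kaplan–Meier estimation, "and analyzed using log-rank test". Neither the sample-size section nor the methods section says whether the test is one- or two-sided, and no sample-size formula is named.

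The follow-up horizon is described in two ways. The abstract says "All patients will be followed up for 60 months after randomization"; Study setting {9} and Provisions for post-trial care {30} also give 60 months. Plans for assessment and collection of outcomes {18a} instead makes 60 months a minimum. Recruitment {15} expects 80 patients a year. Trial status gives a start in November 2019 and possible completion in December 2027.

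**The concern.** A sample size presented as following from stated inputs should be reproducible from them. An unqualified 5% level in a phase III superiority comparison is ordinarily read as two-sided. On that reading, with 5-year rates and 60 months of follow-up, the usual formulas all ask for more than 88 per group once the 5% dropout is added.

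Two things are at stake. Readers are told that the risk of missing a true 15-point difference is 20%, when on the planned 60-month horizon it is nearer 25%. And with sidedness unstated, the rule for declaring significance is not fixed in the published plan.

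**Working it through.** **Inputs.** Death by 5 years 0.25 and 0.10, mean 0.175; 5% dropout; 1:1 allocation; 80% power (Sample size {14}, Trial design {8}). Under proportional hazards, HR = ln 0.90 / ln 0.75 = 0.366 and ln HR = −1.004. z-values: 1.960 (two-sided 5%), 1.645 (one-sided 5%), 0.842 (80% power).

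**Reproducing 88, one-sided.** Freedman log-rank events: (1.645 + 0.842)² × ((1 + 0.366)/(1 − 0.366))² = 28.7, rounded to 29. Patients per group: 29/(2 × 0.175) = 82.9, rounded to 83. With dropout: 83/0.95 = 87.4, rounded to 88. This matches, but only with rounding at each step; unrounded it is 82.1/0.95 = 86.4, so 87. The one-sided two-proportion formula gives 79, then 84, and does not match.

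**Two-sided 5%, everyone followed for 60 months.**

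| Method | Per group | After /0.95 |
|---|---|---|
| Schoenfeld log-rank: 4 × (1.960 + 0.842)²/1.004² = 31.1 events; /0.35 | 88.9 | 93.6, so 94 |
| Two proportions, pooled: [1.960√(2 × 0.175 × 0.825) + 0.842√(0.1875 + 0.09)]²/0.15² | 99.5, so 100 | 105.3, so 106 |
| Freedman log-rank: 36.5 events; /0.35 | 104.2 | 109.7, so 110 |

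Rounding events up first adds one or two to the Freedman figure; a continuity correction takes the two-proportion figure to 119. None gives 88. A log-rank simulation with constant hazards and 5% loss spread over 5 years reached 79.1% power at 98 per group and 81.2% at 100.

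**Power of 88 per group, two-sided 5%, 60 months.** With 88 × 0.95 ≈ 84 evaluable per group:

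- Two proportions: 72.9%
- Freedman: 71.1%
- Schoenfeld: 77.7%
- Simulated log-rank, 88 randomised with 5% loss: 75.0%

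Expected deaths: 176 × 0.175 ≈ 31, or 168 × 0.175 ≈ 29 after dropout.

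**Reproducing 88, two-sided, with longer follow-up.** November 2019 to December 2027 is about 8 years. If each patient has at least 5, accrual could last about 3 years. With uniform accrual and constant hazards, the mean event probability rises from 0.175 to 0.2195. Freedman: 36.48/(2 × 0.2195) = 83.1; /0.95 = 87.5, so 88 (rounding up earlier gives 89 or 90). Lachin–Foulkes with unpooled variance: 83.3; /0.95 = 87.7, so 88.

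Two-sided Schoenfeld at 60 months with the dropout step omitted also comes close, at 88.9.

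**Power of 88 per group if all follow-up is used.** The stated recruitment rate gives 176/80 = 2.2 years of accrual. Simulated two-sided log-rank power with 5% loss is 81.8% if follow-up ends 5 years after the last entry, and 86.5% if it runs to December 2027. With OS capped at 60 months in that same setting it returns to 75.4%.

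**The case against.** The best defence is that the shortfall depends on the horizon. The OS definition in Outcomes {12} runs to death or last follow-up and has no cap, whereas relapse-free survival in the same section is limited to 60 months. Section {18a} allows follow-up beyond 60 months, and a log-rank test uses all the time it is given. On that reading two-sided power is about 82–86% and the claimed 80% is met. It can also be said that a journal article often leaves the formula and accrual inputs to the full protocol.

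Part of this stands. The shortfall is conditional on a two-sided test and a 60-month horizon, so a flat statement that the trial's true power is below 80% would go too far. It does not clear the section, though: the calculation is built on 5-year rates for a 5-year endpoint, three places give 60 months of follow-up, and no accrual or longer observation period enters the stated inputs. Nor is this only an omitted detail, because a figure is published as following from inputs that do not yield it on the ordinary reading.

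A reader might also infer from the one-sided match that an undeclared one-sided 5% test was used, with twice the conventional 2.5% chance of falsely claiming superiority. The document does not support that. Two-sided calculations with longer follow-up reach the same number, and each match depends on the choice of formula and rounding.

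**Conclusion.** The point holds in conditional form. For a two-sided 5% log-rank test with OS assessed to 60 months, 75% versus 90% survival and 5% loss, 88 per group gives about 73–75% power (71–78% across standard formulas), a shortfall of roughly 5 to 7 points from the stated 80%. About 100 per group (simulation) to 106 (pooled two-proportion formula) would be needed.

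If all follow-up to 5 years after the last entry is analysed, power is about 82%; that assumes uniform accrual over 2.2 years and constant hazards. The article does not settle which horizon applies, does not state sidedness, and does not allow the origin of 88 to be determined.

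**What to change.** In Sample size {14} and Statistical methods {20a}, state that the primary log-rank test is two-sided at 5%; if a one-sided 5% test was intended, declare it. Name the sample-size formula and the expected number of deaths (about 30 at 60 months).

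State whether OS is censored at 60 months or analysed on all follow-up, and reconcile the abstract, {9} and {30} with {18a}. Then restate the power of 176 patients to match: about 75% with a 60-month cap, or about 82% with every patient followed until 5 years after the last entry and all that time used, giving the accrual and hazard assumptions.

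The cost is a few sentences and, under the 60-month cap, a less favourable stated power. No further patients need be enrolled to make the statement correct.

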### Recruitment {15}

All patients with cN0-pT1b ESCC diagnosed after ESD treatment are potential candidates in this trial. The endoscopists will register all of these patients and notify the clinical research coordinator (CRC) of this trial, and the CRC will contact and tell potential candidates about this trial. After screening for the eligible criteria, the CRC will set up a meeting with potential candidates or their authorized surrogates and [name] in the outpatient clinic. [name] will explain the details of this trial to them and obtain their signatures.

The three institutions which are participating in this trial are high-volume medical centers with esophagectomy and ESD treatment. According to our estimation of the duration of recruitment, 80 patients will be recruited per year.

### Assignment of interventions: allocation

#### Sequence generation {16a}

The allocation sequence is according to the computer-generated random numbers.

#### Concealment mechanism {16b}

Sealed envelopes will be used in implementing the allocation sequence.

#### Implementation {16c}

The CRC of the Ad-ESD trial will generate the allocation sequence. A clinical physician will be in charge of the enrolment of participants and assign participants to each intervention. The assignment of interventions is not blinding.

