#### Procedure for unblinding if needed {17b}

This trial is an open-label RCT with only statistical analysts being blinded to the procedure and the results of randomization, group allocation, and intervention.

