#### Data management {19}

Data will be entered into online encrypted database and a separate Excel form from the CRC staff. Researchers must have an authorized account to access the database.

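### The clinical research coordinator generates the allocation sequence and also approaches candidates, so allocation is not concealed from that role

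*Protocol article*

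**What the plan says.** Four sections of the protocol article bear on this.

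- **Sequence generation {16a} and Implementation {16c}.** The list is computer-generated: "The allocation sequence is according to the computer-generated random numbers". Its author is named: "The CRC of the Ad-ESD trial will generate the allocation sequence". Enrolment and assignment belong to someone else: "A clinical physician will be in charge of the enrolment of participants and assign participants to each intervention".
- **Concealment mechanism {16b}.** One device is given: "Sealed envelopes will be used in implementing the allocation sequence".
- **Recruitment {15}.** Endoscopists register every patient found to have cN0-pT1b disease after ESD and notify the CRC. Then "the CRC will contact and tell potential candidates about this trial", and "After screening for the eligible criteria, the CRC will set up a meeting with potential candidates or their authorized surrogates". Another role attends that meeting, explains the trial and obtains the signature.
- **Procedure for unblinding {17b}.** "This trial is an open-label RCT with only statistical analysts being blinded to the procedure and the results of randomization".

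**The concern.** Allocation concealment requires that nobody who can influence whether or when a candidate enters the trial knows the next assignment. Generating the list and recruiting from it are the two tasks to keep apart, and here the text gives both to one named role.

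The setting gives such knowledge some force. The Discussion says that the choice between these two treatments used to follow patient and doctor preference, and it expects recruitment to be difficult because the interventions and their costs differ. Eligibility is prognostically broad: age 18 to 75, ECOG 0 to 2, and positive lateral margins allowed. A coordinator who knew the next assignment could, even without intent, bring a contact or meeting forward or put it back, or present the trial differently.

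What is at stake is the primary comparison, overall survival in all randomised patients by log-rank test. Its validity rests on randomisation. Intention-to-treat keeps patients in the groups to which they were allocated, but it cannot correct groups whose make-up was influenced beforehand.

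**Working it through.** The point concerns separation of roles, so there is no figure in the plan to reproduce. The check sets the sections side by side.

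| Step | Who does it | Section | Can this role know the next assignment? |
|---|---|---|---|
| Register all candidates | Endoscopists | {15} | Not shown |
| First contact, telling candidates about the trial | CRC | {15} | Yes, as author of the list |
| Eligibility screening | Not expressly named | {15} | Depends on who screens |
| Arrange the consent meeting | CRC | {15} | Yes, as author of the list |
| Explain details, obtain consent | Another role | {15}, {26a} | Not shown |
| Enrol and assign | A clinical physician | {16c} | Not shown; the envelopes are meant to prevent it |
| Generate the sequence | CRC | {16c} | Yes, by definition |

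1. Sealing an envelope hides its content from people who have not seen the list. It does nothing for the person who produced the list, so {16b} does not protect against the role named in {16c}.
2. That role has two tasks in {15} that affect the timing and flow of candidates towards enrolment.
3. No section names an independent generator, a separate holder of the list or a central allocation service. {17a} and {17b} blind only the statistical analysts.
4. Hence allocation is not concealed from the CRC.

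**Size.** The shift in the 5-year survival difference with no treatment effect would be roughly (difference between arms in the share of poor-prognosis patients) × (difference in 5-year survival between poor- and good-prognosis patients). The document gives neither factor, so no estimate is offered. The only yardstick it supplies is the design difference under Sample size {14}: 90% − 75% = 15 percentage points.

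**How far a baseline check can help.** With 88 per arm, the standard error of a between-arm difference in a characteristic of prevalence p is √(2p(1−p)/88). Taking p = 20% to 40% as an assumption:

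- p = 0.20: √(0.32/88) = 0.060, so a 10-point imbalance is 0.10/0.060 ≈ 1.7 standard errors.
- p = 0.40: √(0.48/88) = 0.074, so a 10-point imbalance is 0.10/0.074 ≈ 1.4 standard errors.

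Chance alone could produce an imbalance of that size. A baseline table can raise suspicion but cannot rule selection in or out.

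**Timing.** Recruitment began in November 2019 (Trial status) at an expected 80 a year ({15}). At that rate 176/80 = 2.2 years are needed. Actual accrual is not given.

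**The case against.** The strongest reply is that the protocol does separate several steps. Endoscopists register all potential candidates, so the CRC is not described as choosing whom to approach, and the register could be used to audit who was and was not enrolled. Another role takes consent. A physician enrols and assigns from envelopes, which is ordinary practice and no breach unless that physician knows the list. Nothing says the CRC shares it. The CRC function may also be held by several people, since Data management {19} speaks of CRC staff.

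Much of this stands, and it limits the point. A reader might infer that allocation is open to recruiting staff in general; the document does not show that. A reader might infer that the CRC screens; that is the natural reading of the sentence in {15}, but the screener is not expressly named. Envelope opacity, numbering and custody are details an article commonly leaves to the full protocol, so their absence is not a fault here. The CRC's later follow-up contact under {20c} has no bearing on concealment.

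None of this removes the overlap. The register limits silent omission but does not govern the timing of contact or meetings. If several people act as CRC, the text uses one term for both tasks and states no division between them. More detail about the envelopes would not help, because the author of the list would still know it.

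**Conclusion.** The concern holds for the CRC and no further. The plan assigns list generation and candidate contact to one role, and its only concealment device cannot work against that role. This is a stated rule that admits selection bias, not a detail lost in condensing the article.

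The conclusion rests on reading the term CRC as the same role in {15} and {16c}, with no unstated split of duties. The size of any bias cannot be computed from the document, and nothing shows that bias has occurred. The case for change rests on principle: the fault is cheap to remove before randomisation and cannot be repaired in the analysis.

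**What to change.** Amend Implementation {16c} so that the sequence for all patients still to be randomised is generated and held by someone with no contact with candidates. The project management group is one option: the auditing section {23} describes it as working independently of investigators and sponsor. Confirm first that the person chosen has no recruitment duties. The blinded statistical analysts are not suitable as things stand, because {17a} and {17b} keep them unaware of the randomisation procedure and results.

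Release each allocation only after consent and eligibility are recorded. Central release would be preferable if the online system can support it, but Data management {19} describes that system only for data entry ("Data will be entered into online encrypted database"). Otherwise, envelopes prepared by the independent person would close the gap, so envelopes need not be abandoned.

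For patients already randomised, report who generated and held the list and check baseline balance, bearing in mind the limited information in such a check. If recruitment is complete, this part is all that remains to be done.

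The cost is a short protocol amendment and a small reassignment of duties. Treatment, endpoints and sample size are unaffected.

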#### Who will be blinded {17a}

Because of the different interventions in the two groups, the thoracic surgeons or radiologists will not be blinded to group allocation. Statistical analysts will be blind to the procedure and the results of randomization, group allocation, and intervention.

#### Procedure for unblinding if needed {17b}

This trial is an open-label RCT with only statistical analysts being blinded to the procedure and the results of randomization, group allocation, and intervention.

### Data collection and management

#### Plans for assessment and collection of outcomes {18a}

After completion of allocated treatments, patients will be followed up until death or over a period of at least 60 months. All patients will be required to send back the QoL questionnaires at the 1st, 3rd, 6th, 12th, and 24th month after randomization. The CT scan of chest and abdominal and ultrasound of the neck will be performed at 6-month intervals for the first 3 years and every year for the next 2 years after treatment. Positron emission tomography-CT will be used selectively.

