##### Criteria for discontinuing or modifying allocated interventions {11b}

Allocated interventions will not be modified as a rule, except for participants who cannot finish chemoradiation because of severe adverse events.

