#### Strategies to improve adherence to interventions {11c}

Because this is a surgical RCT, there will be no further strategy to improve adherence to interventions.

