#### Provisions for post-trial care {30}

All participants will be followed up over a period of 60 months or until death.

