#### Outcomes {12}

##### Primary endpoint

The primary endpoint is 5-year OS in all randomly assigned patients. OS is defined as the time from the date of randomization to the day of last follow-up or death.

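### Section {18a} counts follow-up and scans from treatment, the abstract and the endpoints count from randomization: untreated patients have no scan calendar, and the arms' scans fall about 5 weeks apart

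*Protocol article*

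**What the plan says.** Section {18a}, which sets how outcomes are collected, opens: "After completion of allocated treatments, patients will be followed up until death or over a period of at least 60 months". Its CT and neck ultrasound examinations are to be "performed at 6-month intervals for the first 3 years and every year for the next 2 years after treatment". Study setting {9} likewise places the 60-month follow-up after the intervention.

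Other current text uses a different clock or sets no treatment condition:

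- Abstract, Methods: "All patients will be followed up for 60 months after randomization".
- Provisions for post-trial care {30}: "All participants will be followed up over a period of 60 months or until death".
- Section {18b}: telephone follow-up every 3 months, with no treatment condition.
- Section {18a} itself, for quality of life: "All patients will be required to send back the QoL questionnaires at the 1st, 3rd, 6th, 12th, and 24th month after randomization".
- Outcomes {12}: "The primary endpoint is 5-year OS in all randomly assigned patients". OS and RFS are both timed from randomization, and RFS is assessed up to 60 months.

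The protocol foresees incomplete treatment. Section {11b} allows no modification of the allocated intervention "except for participants who cannot finish chemoradiation because of severe adverse events", and section {20a} plans a per-protocol analysis beside the intention-to-treat one.

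**The concern.** An endpoint timed from randomization in everyone randomised needs an assessment calendar that exists for everyone randomised and runs on the same clock in both arms. The calendar in {18a} does neither. It depends on an event after randomization that some patients will not reach, and that completers reach at different times according to arm.

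At stake is the recurrence and progression component of RFS, which these scans are there to detect. If a site has no date from which to schedule scans for a patient who never had the operation, recurrence in that patient is found late, by symptoms, or not at all. The intention-to-treat principle named in {20c} cannot recover an event that was never looked for. Among completers, scan dates that differ systematically by arm make the recorded recurrence date depend partly on the calendar.

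**Working it through.** The plan gives no figure for this point, so the first step compares passages and the rest uses the plan's own treatment schedule.

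**1. Which clock each passage uses**

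| Item | Counted from | Covers all randomised patients? |
|---|---|---|
| Follow-up, abstract | randomization | yes |
| Follow-up, {30} | not stated | yes |
| Telephone contact, {18b} | not stated | no treatment condition |
| QoL forms, {18a} | randomization | yes |
| OS and RFS, {12} | randomization | yes for OS; not restricted for RFS |
| Follow-up, {9} | after the intervention | not addressed |
| Follow-up, {18a} | completion of allocated treatment | not addressed |
| CT and ultrasound, {18a} | treatment | not addressed |

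Follow-up for death has an alternative anchor in the abstract. The scan calendar has none anywhere in the document.

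**2. Patients without a usable scan date**

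- No treatment received: no date exists.
- Chemoradiotherapy stopped early: the count could start at the last fraction given, the last chemotherapy, or the planned end. The text does not say which.
- Switch of arm: the count could start from the treatment received, but the opening sentence speaks of the allocated one.

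**3. Offset between arms among completers**

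Inputs: 28 fractions, 5 days per week (dCRT description); both interventions start about 3 weeks after ESD ({9}). The plan's fraction count agrees with its doses: 6020/215 = 28 and 5040/180 = 28.

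- Duration: 28/5 = 5.6 weeks. Counted from first to last fraction, with a Monday start and no interruption, this is 5 × 7 + 2 = 37 days, or 37/7 = 5.3 weeks.
- Surgery is a single procedure, so its completion is taken as the day of operation.
- With equal start dates, every dCRT scan falls about 5.3 to 5.6 weeks later from randomization than the matching surgical scan. Taking 6 months as 26 weeks, that is 5.6/26 = 21.5% of the interval.

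**4. What the offset does to recorded recurrence dates**

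Assume that recurrences arise evenly between scans and are found only by scans.

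- After the first scan, a share (26 − 5.6)/26 = 78.5% is dated 5.6 weeks later under the dCRT calendar.
- The other 21.5% is dated 26 − 5.6 = 20.4 weeks earlier, because the next surgical scan has yet to come.
- Average shift: (20.4/26) × 5.6 − (5.6/26) × 20.4 = 0.
- Before the first scan there is no such balance: a recurrence arising before the first surgical scan is always dated 5.6 weeks later under the dCRT calendar.

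Recorded dates therefore differ by arm, but the effect has no single sign.

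**5. Landmarks**

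Treatment follows randomization, so a scan 36 months after treatment falls after month 36 from randomization in both arms. The last scan before the 3-year landmark is then the month-30 one, and in the dCRT arm it looks about 5 weeks further forward. By the same reasoning the final scan, 5 years after treatment, falls beyond the 60 months to which RFS is assessed.

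**The case against.** The strongest reply is that the opening of {18a} describes a sequence, treatment and then follow-up, and does not make completion a condition for being followed. The abstract, {30} and {18b} cover everyone, the primary endpoint is stated for all randomised patients, and {20c} censors only patients who are lost to follow-up. A non-completer who is still telephoned is not lost. This stands. A reader might infer from {18a} that non-completers drop out of the OS analysis and that the survival comparison becomes one of completers. The documents do not support that: death can be ascertained through the three-monthly contact. Any figure for such a bias would need an assumed share of non-completers, an assumed survival for them, and an assumption about loss in each arm, none of which the protocol gives.

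Second, the scan sentence refers to treatment in general, so most early stoppers have some end date, and inability to accept a treatment component is excluded at screening. This narrows the group but does not close the gap. Screening does not govern what happens after randomization, and the absence of further adherence measures in {11c} ("there will be no further strategy to improve adherence to interventions") concerns treatment, not follow-up, so it neither worsens nor solves the problem.

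Third, an article condenses the full protocol, and visit rules for off-treatment patients may be there. That is fair for an omission. It does not explain two current passages that state different clocks, nor the offset between arms, which follows from what is printed.

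**Conclusion.** The point holds as an inconsistency of clocks with a consequence for RFS. Sections {18a} and {9} count from treatment; the abstract and both survival endpoints count from randomization. The scan calendar has no anchor for a patient who receives no treatment and an ambiguous one for a patient who stops chemoradiotherapy early. Among completers, dCRT scans fall roughly 5 weeks later from randomization than surgical scans, about a fifth of a 6-month interval. This size assumes equal start dates in the two arms, uninterrupted radiotherapy, and the operation date as the end of surgical treatment.

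The documents give neither the number of patients without an anchor nor a net RFS bias. It may be tempting to read the offset as favouring dCRT, but the shifts run both ways, so no direction is established. No bias in OS is shown. The point concerns a secondary endpoint and should be corrected because the correction is cheap and missed scans cannot be made up later.

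**What to change.** Reconcile the abstract, {9} and {18a}. Replace the opening of {18a} with text such as: *Every randomised patient, including those who do not start, do not complete or switch the allocated treatment, is followed from randomization to death or for at least 60 months. CT and ultrasound follow the same calendar, counted from randomization, in both arms. Stopping or switching treatment is not withdrawal from follow-up.* Keep the existing scan intervals, and align {9} with this wording.

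Counting from randomization also places scans at the 3-year and 5-year landmarks.

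The cost is an amendment, a site instruction, a few routine scans for non-completers, and a small shift in scan dates. The first dCRT scan would come closer to the end of treatment than now planned; the investigators should confirm that this is acceptable for assessment. The timetable is not lengthened: 176 patients at 80 per year is 176/80 = 2.2 years from November 2019, so 60 months from the last randomization ends around early 2027, before the anticipated completion in December 2027.
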